### 2.3. Analysis (Phases 3–5)

Qualitative data from people with SMI and bereaved caregivers’ interviews (Phase 3), multi-disciplinary focus groups (Phase 4) and co-design workshops (Phase 5) will be analysed using thematic analysis, with each phase of analysis conducted independently. This inductive approach to analysis will follow the six stages outlined [54]. Step 1 involves familiarisation with the data; it will start with listening to the digital recordings and reading the transcripts for accuracy, followed by reading and re-reading the transcripts to become familiar with the data. Stage 2 will generate initial codes; these will be developed through assigning a phrase or concept to a portion of the data to define its meaning in relation to the data generated and the research aim [55]. Stage 3 will begin when all data have been initially coded and collated and will search for themes within the data by considering how different codes combine together to form themes. Stage 4 will review themes and refine them to ensure they clearly explain the data collected. Stage 5 is to clearly define what each theme is, and what it is not, by developing names (descriptive labels) for each theme. Finally, stage 6 will begin when the research team has a set of fully worked-out themes. This stage involves telling the complicated story of the data in a way which convinces a reader of the merit and validity of the analysis. The importance of providing a coherent, nonrepetitive account of the data and thoughtfully selecting quotations to represent the findings is recognised [54]. In each stage of data analysis, the lead researcher (MT) will work closely with team members ([name] and [name]) who will read a proportion (30%) of the transcripts and independently code them, the appropriateness of which is outlined in the literature [56]. NVIVO will be used for Phases 3–5 data management [57]. All data display tables and any visual representations of the evolving codes and themes within NVIVO will be retained for the audit trail of this analysis.

### 2.4. Rigour

The criteria proposed by Lincoln and Guba [58] for evaluating qualitative research will be used in this study to increase credibility, transferability, dependability and confirmability. To ensure credibility in the study, reflective questioning will be used in both the qualitative interviews and focus groups. The research team will reflect on their interpretation of the participants′ answers, throughout the interviews/focus groups, to capture the meaning the participants were hoping to convey. Data (multiple key informants) and space (two recruitment sites) triangulation will also take place [59] and this will enhance credibility. Transferability of the results generated in the study will be achieved through ‘thick description’ [58]. This will entail providing explicit accounts of the experiences of the participants and not just detailing surface interpretations, but uncovering the meaning behind their feelings and actions as well [60]. Auditing will be used to establish dependability and confirmability of the study [58], such as the audit trail discussed within the analysis section.

### 2.5. Ethical Considerations

The study will be conducted in compliance with Good Clinical Practice Guidelines, with ethical and governance permissions from both recruitment sites. In addition, fundamental principles of good practice, including the provision of user-friendly information sheets, written informed consent, voluntary participation, the opportunity to withdraw from the study at any time and confidentiality and data protection procedures, will be applied as a minimum standard. As sensitive issues may be identified and discussed during the semi-structured interviews and focus groups, it is acknowledged that potential respondents may become distressed/upset. The research team will develop and use a distress protocol [61] within this study. As part of this distress protocol, post-interview, all patients and bereaved carers will be provided with information packs on support services. If required, they can self-refer to these services. Additionally, with participants’ consent, general practitioners will be advised that they have taken part within the study. As it is anticipated that interviews may be conducted in patients and carers homes (subject to COVID-19 restrictions), a lone worker policy [62] will be used within the study.

## 3. Discussion

This paper describes the study protocol of an evidenced informed service model of integrated palliative care for people living with an SMI. The main intention is that through raising awareness and facilitating the co-design of an evidenced based service model, the needs of service users and their caregivers from this marginalised overlooked group will be recognised and responded to within the model of integrated palliative care.

Globally mental health is a burden, in the United Kingdom, one in six of the population will require treatment for mental illness in their lifetime [63]. Large inequalities and gaps in care of people with mental illness exist, and this is a key indicator for health and wellbeing [15]. This research plans to significantly address health inequalities for people with SMI by illuminating the experiences of people with SMI, and bereaved caregivers and health care professionals to develop a co-designed service model of integrated palliative care. This will be done collaboratively with key stakeholders within the expert reference group, which includes people who experience these disparities in relation to accessing palliative care, bereaved caregivers and professional caregivers. It is anticipated that because of this study, service provision for people with SMI in need of palliative care will see a cultural shift in both public and professional awareness in relation to this vulnerable group.

## Figures and Tables

**Figure 1 healthcare-09-01710-f001:**
[figure not shown]
Overview of the six stages of the study.

**Table 1 healthcare-09-01710-t001:** Inclusion and exclusion criteria for Phase 3 participants.

**People with Severe Mental Illness.**	
**Inclusion Criteria**	**Exclusion Criteria**
Diagnosis of severe mental illness (as per operational definition)	No diagnosis of severe mental illness
Currently receiving palliative care	Not receiving palliative care
Over 18 years of age	Under 18 years of age
Capacity to take part in the study—as determined by the clinical gatekeeper	Does not have capacity to take part—as determined by the clinical gatekeeper
Can understand and speak English	Not fluent in English
**Caregivers**	
**Inclusion Criteria**	**Exclusion Criteria**
Bereaved caregiver of a patient with severe mental illness who has died 6–18 months earlier	Bereaved carer of patient who had died and not had a severe mental illness
Over 18 years of age	Under 18 years of age
Can understand and speak English	Not fluent in English

**Table 2 healthcare-09-01710-t002:** Inclusion and exclusion criteria for Phase 4 participants.

Inclusion Criteria	Exclusion Criteria
Healthcare professionals involved in the care of people who have a severe mental illness and or palliative care	Healthcare professionals not involved in either severe mental illness or palliative care delivery
Employed within the recruiting Health and Social Trusts	Have a non-permanent contract with the Health and Social Trust, e.g., agency staff
Have an appropriate professional qualification in their field of work	Not fluent in English
Can understand and speak English	

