## Abstract

Background: Globally, close to one billion people are living with a mental health disorder, and it is one of the most neglected areas in Public Health. People with severe mental illness have greater mortality risk than the general population, experience health care inequalities throughout life and represent a vulnerable, under-served and under-treated population, who have been overlooked in health inequality research to date. There is currently a dearth of evidence in relation to understanding the palliative care needs of people with severe mental illness and how future care delivery can be designed to both recognise and respond to those needs. This study aims to co-design an evidenced informed service model of integrated palliative care for persons living with a severe mental illness. Methods: This qualitative sequential study underpinned by interpretivism will have six phases. An expert reference group will be established in Phase 1, to inform all stages of this study. Phase 2 will include a systematic literature review to synthesise current evidence in relation to palliative care service provision for people with severe mental illness. In Phase 3, qualitative interviews will be undertaken with both, patients who have a severe mental illness and in receipt of palliative care (n = 13), and bereaved caregivers of people who have died 6–18 months previously with a diagnosis of severe mental illness (n = 13), across two recruitment sties in the United Kingdom. Focus groups (n = 4) with both mental health and palliative care multidisciplinary staff will be undertaken across the two recruitment sites in Phase 4. Phase 5 will involve the co-design of a service model of integrated palliative care for persons living with severe mental illness. Phase 6 will develop practice recommendations for this client cohort. Discussion: Palliative care needs to be available at all levels of care systems; it is estimated that, globally, only 14% of patients who need palliative care receive it. Reducing inequalities experienced by people with severe mental illness is embedded in the National Health Service Long Term Plan. Internationally, the gap between those with a mental illness needing care and those with access to care remains considerable. Future policy and practice will benefit from a better understanding of the needs of this client cohort and the development of a co-designed integrated care pathway to facilitate timely access to palliative care for people with a severe mental illness.

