Phase 3: this includes qualitative semi-structured interviews with both people who have SMI in current receipt of palliative care and bereaved caregivers of people with SMI. As previously outlined, many people with SMI do not access palliative care, and for those that do, who may be at the end stage of their lives, taking part in research may be difficult due to the increased deterioration and symptom burden. Recruiting only people with SMI as participants in palliative care research has the potential to be biased, as the patient may only be able to take part in the research if they are relatively well [29]. The challenges faced by people who are increasingly debilitated due to the impact of their disease may not be fully captured within the data. This is a complex recruitment challenge and the research team will adopt a two-pronged approach to data collection, recruiting both people with SMI currently in receipt of palliative care and bereaved caregivers of people with SMI. Bereaved caregivers have been chosen to be involved in this study as proxies for people with SMI in receipt of palliative care to provide vital insight into the person with SMI end-of-life care. Evidence shows that such proxies can reliably provide information on the person’s experience and quality of palliative care services and on patient’s symptoms at the end of their life [30,31]. By using this combined recruitment strategy, it is envisaged that the research team will gain a full understanding of the totality of the experience of palliative care provision for people with SMI. Caregiver participants will be recruited 6–18 months post-bereavement. The period of time post bereavement has been given careful consideration, and although this was not straight after the death of the person with SMI, it is within a time-frame which previous research has demonstrated allows bereaved caregivers to remember their experience, whilst minimising trauma to the participant [30] and giving due consideration to the ethical concerns when approaching bereaved caregivers [32]. Inclusion and exclusion criteria are detailed in Table 1 below.

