We will conduct approximately 13 interviews with each group, i.e., people who have an SMI and are currently in receipt of palliative care and bereaved caregivers of people who have had an SMI. As this is an exploratory qualitative study, the final sample size will be determined by data saturation, the appropriateness of which is outlined in the literature [33]. The principle of 10 + 3 for data saturation outlines a minimum of 10 interviews should be conducted, followed by at least three consecutive interviews that present no new findings [34]. Thus, sample size will be determined by ‘information redundancy’ [35]. Recruitment will be from two Health and Social Care Trusts within the United Kingdom.

People with SMI currently in receipt of palliative care will be invited to take part in this research via a clinical gatekeeper. Gatekeepers are responsible for ensuring ethical standards are adhered to when selecting potential participants [36]. In this instance, the gatekeepers will be psychiatrists and community psychiatric nurses in each Health and Social Care Trust. Contact will be via outpatient clinics and domiciliary visits, while gatekeepers will provide (1) an invitation letter to take part in the study, (2) a participant information sheet and (3) a consent to be contacted form, which will be returned to the research team via a pre-paid envelope.

Bereaved caregivers will be invited to take part in this research via the lead community psychiatric nurses and a mental health caregivers advocacy group in each recruitment site. These individuals will act as gatekeepers to identify potential participants and contact them to invite them to take part in this study. Contact with potential bereaved caregiver participants will be via post; gatekeepers will provide (1) an invitation letter to take part in the study, (2) a participant information sheet and (3) a consent to be contacted form, which will be returned to the research team via a pre-paid envelope.

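### The Table 1 caregiver criteria do not secure the palliative care proxies that the Phase 3 rationale relies on

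*Protocol article*

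**What the plan says.** The protocol article gives the caregiver group its purpose in Section 2.2 (Phase 3): "Bereaved caregivers have been chosen to be involved in this study as proxies for people with SMI in receipt of palliative care". The same paragraph explains the need. Patients near the end of life may be too ill to take part, so a patient-only sample would lean towards those in better health. It then relies on evidence that "such proxies can reliably provide information on the person’s experience and quality of palliative care services", and on symptoms at the end of life.

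Table 1 sets the eligibility rule. The inclusion row for caregivers reads "Bereaved caregiver of a patient with severe mental illness who has died 6–18 months earlier". The matching exclusion is "Bereaved carer of patient who had died and not had a severe mental illness". The remaining rows concern age and English. In the patient half of the same table, by contrast, "Currently receiving palliative care" is an inclusion criterion.

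Caregivers are to be found through "lead community psychiatric nurses and a mental health caregivers advocacy group in each recruitment site". The planned number is about 13 per group, set by the 10 + 3 saturation rule.

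**The concern.** The role and the rule do not match. The role needs someone who can report on palliative care that the deceased received. The rule asks about diagnosis and date of death, and says nothing about palliative care, life-limiting illness or an expected death.

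What is at stake is the two-pronged recruitment. The caregiver interviews are there to offset a bias that the article itself identifies in the patient interviews. A caregiver whose relative had no palliative need cannot do this, yet is eligible. The Phase 3 findings are then presented in the first Phase 5 workshop, where they help to build the service model. Analysis cannot repair the composition of the sample once the interviews are done.

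**Working it through.** No statistical test or power calculation applies. The check is a comparison of passages, with one figure to reproduce.

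**Planned number.** Section 2.2 states the 10 + 3 rule: 10 + 3 = 13, which agrees with the article's approximate figure per group. Caregivers are therefore 13 of 13 + 13 = 26 planned Phase 3 interviews, or half. The number is not in dispute.

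**Rule against role.** A caregiver who meets the SMI, timing, age and English conditions may be bereaved of one of three kinds of person:

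| The deceased with SMI | Eligible under Table 1? | Proxy for a palliative care recipient (Section 2.2)? | Informs access or unmet need (Section 1)? |
|---|---|---|---|
| A. Received palliative care | Yes | Yes | Yes |
| B. Had a life-limiting illness, received no palliative care | Yes | No | Yes |
| C. Died suddenly or with no palliative need | Yes | No | No |

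Table 1 does not separate A, B and C. Only A fits the role stated in Section 2.2. C falls outside the study question altogether.

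**Does another part of the article close the gap?**

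1. The Abstract describes caregivers by the SMI diagnosis of the deceased and the 6–18 month window only.
2. The sample-size text in Section 2.2 describes them by SMI only.
3. The recruitment route names mental health gatekeepers and no palliative care service, so it does not select for A.
4. The caregiver exclusions remove no one in B or C.

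None of these supplies the missing condition. The patient rows show that the authors did write a palliative care condition where they wanted one.

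**Is group B or C foreseeable?** For B, yes: Section 2.2 says that "many people with SMI do not access palliative care". For C, the documents are silent on frequency; the point is only that the rule lets such caregivers in.

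**Size.** If a share p of the interviewed caregivers belongs to A, the expected number of proxies is 13 × p. The documents give no value of p for people with SMI, for the United Kingdom, or for caregivers reached by this route, so the product cannot be evaluated. Each interview outside A is 1/13, or about 8%, of the planned caregiver group.

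**The case against.** The strongest defence is that the caregiver role is wider than the word proxy suggests. Section 1 wants caregivers to describe barriers to palliative care, and Section 2.2 also mentions end-of-life care and symptoms in general. A caregiver of someone who needed palliative care and never received it is informative on these, and a rule requiring receipt would remove the accounts of the most under-served. This stands, and it is why the fix should not require receipt. It does not turn group B into proxies for recipients, and it offers nothing for group C.

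A second defence is that this is an exploratory qualitative study with no estimate to bias, that off-topic interviews would be visible in the transcripts, and that 13 is approximate. This also stands in part, and it lowers the severity. It does not remove the mismatch between an itemised eligibility table and the rationale printed in the same article, so the gap is not mere condensation.

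A reader might infer several stronger things that the documents do not support:

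- **That many or most caregivers could not act as proxies.** The Abstract says that "globally, only 14% of patients who need palliative care receive it", and 13 × 0.14 = 1.8 looks like an answer. But that figure is global and applies to patients in need. It is neither an SMI nor a United Kingdom rate, and gatekeeper-led, self-selecting recruitment is not random sampling. It estimates nothing about this sample.
- **That the SMI status of the deceased is left undefined.** Section 2.1 gives an operational definition for the whole study, so its absence from the caregiver row is no gap.
- **That unsuitable accounts would be merged with patient accounts.** Section 2.3 says that each phase is analysed independently and does not say how the two Phase 3 groups are combined.
- **That saturation must be reached separately among recipients' caregivers.** Nothing in the article calls for this, and it could demand many more interviews.

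**Conclusion.** The concern holds in a limited form. The caregiver rule does not guarantee the proxies that the Phase 3 rationale depends on, and it admits caregivers of people who died suddenly or with no palliative need. This follows from the text alone and rests on no assumed rate. How many of the 13 would be affected is unknown; the documents support neither a count nor the word many. Caregivers of people who had palliative need but no palliative care remain useful for questions of access, though not as proxies.

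This should be fixed, but it does not threaten the study as a whole. The conclusion assumes that Table 1 is the operative rule and that gatekeepers apply no further, unstated condition.

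**What to change.** Reconcile the Phase 3 rationale in Section 2.2 with the caregiver rows of Table 1, before recruitment:

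1. Add to the caregiver inclusion row that the deceased had a known life-limiting illness (palliative need). This removes group C.
2. Record at screening whether the deceased received palliative care, for example on the consent-to-be-contacted form. This separates A from B.
3. Report the accounts of recipients' caregivers (proxy accounts) distinctly from those of non-recipients' caregivers (access and unmet need).
4. Restate the caregiver role in Section 2.2 so that it covers both.

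Steps 2 to 4 are needed because step 1 alone still admits caregivers of people who never received palliative care. The planned number and the saturation rule can stay as they are.

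The cost is one table line, one screening question, a few words in Section 2.2 and a minor ethics amendment. The downside is a somewhat smaller pool of eligible caregivers.

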## Data Availability

Data is not yet avialable in this study.
